### 3.6. Assessment of perioperative blood glucose variability

After written informed consent is obtained, a subcutaneous glucose sensor Abbott® FreeStyle Libre Pro will be applied in the fatty part of the back of the upper arm of included patients, as recommended by the manufacturer. The Abbot® FreeStyle Libre Pro glucose sensor will allow to measure the baseline BG variability during at least 2 consecutive days prior to surgery using the following parameters: the standard deviation (SD) of BG, the coefficient of glycemic variability (CV) (defined as the ratio of the SD on the mean BG expressed as a percentage), the mean of the daily differences between the higher and the lower values of BG (MAGE), the glycemic lability index and the glycemic penalty index. In case of accidental removal of the sensor during this period or delayed surgery > 14 days after the inclusion, patients will be informed to bring back the sensor the day before surgery so that all blood glucose measurements stored in the sensor can be collected.

The subcutaneous glucose sensor Abbott® FreeStyle Libre Pro will be changed the day before surgery and applied in the same area to measure postoperative BG variability up to 7 days after surgery using the same parameters as preoperatively.

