## 2. Objectives

The primary objective is to describe the relationship between baseline (preoperative) and postoperative BG variability within 48 hours after surgery.

Secondary objectives are: to describe the relationship between baseline and postoperative BG variability within 48 hours after surgery according to the diabetic status and to the type of surgery; to describe the relationship between the preoperative activity of the ANS and the baseline BG variability; to describe the relationship between the preoperative activity of the ANS and the postoperative BG variability within 48 hours after surgery; to describe the relationship between postoperative BG variability within 48 hours after surgery and the postoperative activity of the ANS within 48 hours after surgery; to describe the relationship between postoperative BG variability within 48 hours after surgery and the diabetes phenotype; to describe the relationship between postoperative BG variability within 48 hours after surgery and the urinary and blood level of biomarkers of inflammation and of endothelial dysfunction; and to describe the morbidity and the mortality within 30 days after surgery.

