### 3.8. Outcome measures

The primary outcome will be the mean difference between the preoperative (baseline) and the postoperative CV, and its 95% confidence interval, measured using the subcutaneous glucose sensor Abbott® Free Style Libre Pro.

Secondary outcomes will: the preoperative and postoperative BG variability, quantified by the preoperative and postoperative values of: the SD of BG, the CV, the MAGE, the glycemic lability index and the glycemic penalty index; the preoperative and postoperative activity of the ANS, quantified by the preoperative and postoperative values of: the COMPASS 31 score, the LF, the HF, the LF/HF ratio, the RMSSD, the SDNN, the SDANN, and the pNN50; the diabetes phenotype, described by the preoperative fasting BG and glycosylated hemoglobin values; the blood and urinary levels of biomarkers of inflammation (IL^-^2, IL^-^6, IL^-^10, TNF^-^alpha, 8^-^iso^-^prostanglandin^-^F_2*α*_) and of endothelial function [Endocan, angiopoietin^-^1 (Ang^-^1), angiopoietin^-^2 (Ang^-^2), vascular endothelial (VE)^-^cadherin]; and postoperative morbidity and mortality at day 30 after surgery. Postoperative morbidity includes cardiac arrest, stroke, cardiac arrhythmia requiring therapeutic intervention, surgical wound infection, pneumonia, renal failure requiring dialysis, sepsis, surgical revision, readmission in the intensive care unit or in hospital.

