### 3.11. Sample size calculation

Four groups of patients will be included to describe the relationship between preoperative (baseline) and early postoperative BG variability in diabetic (groups 1 and 2) and non^-^diabetic patients (groups 3 and 4), and between BG variability and the ANS activity in patients treated (groups 1, 2 and 4) or not (group 3) with beta^-^blockers: group 1, including patients with insulin^-^requiring type 2 diabetes mellitus undergoing planned on^-^pump CABG surgery; group 2, including patients with non^-^insulin^-^requiring type 2 diabetes mellitus undergoing planned on^-^pump CABG surgery: group 3, including non^-^diabetic patients undergoing planned aortic valve replacement surgery; and group 4, including non^-^diabetic patients undergoing planned on^-^pump CABG surgery.

No previous study has described the difference between the preoperative (baseline) and the early postoperative CV (primary outcome) in cardiac surgery patients. Thus, no assumption can be made on the expected value of the primary outcome. The sample size calculation was based in the expected measurement accuracy of the primary outcome in each group.

Considering an alpha risk at 0.05 and an estimated standard deviation of CV of 8.2 (basal state) (RE Pratley, 2018 Nov), we hypothesized that the 95% confidence interval range of the difference between the baseline and the early postoperative CV will be no more than 6.12 (conservative assumption considering that the variance will be lower because of the repeated measurement of CV in the same patients). A sample size of 30 patients per group was calculated using the PASS software (“Confidence Intervals for 1 Mean” method, Hahn, G.J. and Meeker, W.Q. 1991. Statistical intervals. John Wiley & Sons. New York).

Thus, the inclusion of a total sample size of 120 patients (30 patients per group) is planned.

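### The index labelled MAGE in Section 3.6 is defined as a mean daily range, so the secondary outcome would carry the name of a different statistic

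*Protocol article*

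**What the plan says.** All references are to the protocol article.

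- Section 3.6 defines the index as "the mean of the daily differences between the higher and the lower values of BG (MAGE". It does not spell out the acronym and gives no excursion threshold or peak-and-nadir rule.
- Section 3.8 makes it a secondary outcome before and after surgery, one of five indices: "the SD of BG, the CV, the MAGE, the glycemic lability index and the glycemic penalty index".
- Section 3.12 uses the variability indices for time trends and for correlations with autonomic activity and biomarkers.
- The baseline sensor is there to "measure the baseline BG variability during at least 2 consecutive days prior to surgery" (Section 3.6), so baseline has a minimum length but no fixed one.
- The objectives in Section 2 concern "baseline (preoperative) and postoperative BG variability within 48 hours after surgery". Section 3.6 also has the second sensor "to measure postoperative BG variability up to 7 days after surgery using the same parameters as preoperatively".
- The text does not say whether a day is a calendar day or a 24-hour block.
- The primary outcome uses another index: "The primary outcome will be the mean difference between the preoperative (baseline) and the postoperative CV" (Section 3.8).

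**The concern.** The article chose to give a formula, and the formula does not match the name, so this is a wrong statement and not a detail left to an analysis plan. An analyst who follows the text will report a daily range under the label MAGE; one who follows the label will compute something else. A reader of the results would set these values beside MAGE values from other work without knowing that they measure something different. The mismatch carries into each secondary analysis in which this index is used.

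A lesser matter follows from the formula itself. A range depends on the length of the segment over which it is taken, so a mean daily range needs a stated day length, applied alike to both recordings. An excursion index is not computed day by day and does not depend on where days are cut.

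**Working it through.** **1. The plan's one calculated figure.** It concerns CV. Section 3.11 gives SD 8.2, a 95% interval of full width 6.12, and 30 patients per group. Width = 2 × t(0.975, 29) × SD / √n = 2 × 2.045 × 8.2 / √30 = 6.12. It reproduces, and the index called MAGE plays no part in it.

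**2. Is the written formula an excursion index?** Two 48-hour traces were built on a flat level of 110 mg/dL.

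| Trace, per day | Mean daily range | Mean of swings of at least one SD |
|---|---|---|
| one rise of 80 mg/dL | 80 | 80 |
| one rise of 80 and three of 40 mg/dL | 80 | about 51 |

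The second excursion mean is close to (80 + 3 × 40) / 4 = 50, as expected. The range sees only the largest swing, whereas the excursion mean sees all that pass the threshold. No swing within a day can exceed that day's range, so for within-day swings the written formula equals or exceeds the excursion mean.

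**3. Size of the gap, and effect of how days are cut.** The inputs are assumed, not taken from the article: stationary first-order autoregressive glucose, mean 130 and SD 30 mg/dL, 15-minute readings, correlation time 1 to 8 h, 4,000 series (400 for the excursion mean). Variability is unchanged throughout. The last five columns give the percentage change in mean daily range, relative to two complete 24-hour blocks, when part-days count as days.

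| Correlation time (h) | Range, 2 × 24 h (mg/dL) | Excursion mean (mg/dL) | 10/24/14 h | 6/24/18 h | 2/24/22 h | Baseline 14/24/10 h | Baseline 14 h, five full days, 10 h |
|---|---|---|---|---|---|---|---|
| 1 | 135.5 | 64.3 | −10.1 | −12.4 | −20.2 | −10.0 | −4.4 |
| 2 | 122.9 | 62.1 | −12.0 | −14.4 | −22.1 | −12.1 | −5.1 |
| 3 | 113.4 | 60.1 | −13.4 | −15.9 | −23.3 | −13.4 | −5.8 |
| 5 | 100.3 | 56.1 | −15.4 | −17.9 | −24.5 | −15.4 | −6.7 |
| 8 | 87.2 | 54.8 | −17.2 | −19.6 | −25.5 | −17.1 | −7.6 |

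- Label: the daily range is 87.2 / 54.8 = 1.6 to 135.5 / 64.3 = 2.1 times the excursion mean.
- 24-hour blocks: two blocks from the end of surgery are the reference, so the bias is zero by construction. Seven blocks differ from two by at most 0.1%. Using only the one complete calendar day inside the 48 h gives a result within 0.2%.
- Calendar days with part-days averaged in: about 10% to 26% low, depending on the cut.
- Before-after contrast, 48-hour baseline: 10/24/14 h after surgery against 14/24/10 h before it differs by 0.1 points or less. Against the same baseline, 6/24/18 h leaves about 2.5 points (for example 12.4 − 10.0 = 2.4). Cancellation therefore needs similar cuts.
- Before-after contrast, baseline over seven calendar days: 10.1 − 4.4 = 5.7 to 17.2 − 7.6 = 9.6, so roughly 6 to 10 points low after surgery for the 10/24/14 h cut.

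**The case against.** On the label: the article never expands the acronym, gives an explicit formula and applies it alike before and after surgery. The index is therefore computable and consistent within the study, and four other indices are reported beside it. That is true and limits the damage. It does not repair the label, because MAGE is the established name of a specific method and the formula given is another one.

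On the part-days: a reader might infer that the postoperative index must read low even when variability is unchanged, so that the before-after change is biased toward a fall. The document does not support this.

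- Nothing in it cuts the window at midnight or averages incomplete days.
- Section 2 counts the postoperative window in elapsed hours, as Section 3.9 does for sampling. The natural reading is two 24-hour blocks, which carry no bias.
- The baseline sensor goes on after consent and is changed the day before surgery, so baseline can also start and end mid-day. Any such effect would then act on both sides.
- Section 3.6 allows postoperative recording of up to 7 days, over which two part-days weigh less.
- How incomplete days are handled is commonly left to an analysis plan.

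These points stand. What remains is that the article does not fix the baseline length, and Section 3.6 contemplates surgery more than 14 days after inclusion. Cancellation would therefore not be assured if calendar days were used. The simulated sizes rest on a simple model that may fit patients on glucose infusion and titrated insulin poorly. Only the direction is free of the model: a range over part of a day cannot exceed the range over the whole of that day.

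**Conclusion.** The definition is wrong for the name it carries. The index in Section 3.6 is a mean daily range, and values reported from it in Section 3.8 would not be MAGE. The constructed traces show this without any distributional assumption (80 against about 51 mg/dL at equal daily range). The ratio of 1.6 to 2.1 rests on the assumed dynamics and on one implementation of the excursion rule.

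A part-day bias is conditional and is not established by the document. It would arise only if calendar days were used and incomplete days averaged in. A net before-after deficit would further need a baseline that is longer than 48 h or cut at clearly different hours.

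The impact is confined to one secondary index in a descriptive study. The CV primary outcome and the sample size of 30 per group are unaffected.

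**What to change.** Make one of two changes in Section 3.6 and carry it through to Section 3.8:

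1. Keep the name MAGE and define it by its excursion algorithm, that is, the mean of peak-to-nadir swings exceeding one SD, computed in the same way on the baseline and postoperative recordings.
2. Keep the formula and rename the index *mean daily range*. Compute it on complete 24-hour blocks in both periods: 0–24 h and 24–48 h after surgery, and 24-hour blocks before surgery. The block rule is a precaution that removes any dependence on clock time.

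Either change costs one sentence and a few lines of code. Both use sensor readings already planned, and neither affects the primary analysis or the number of patients.

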### 3.7. Assessment of the activity of the autonomous nervous system

The baseline activity of the ANS will be measured using the COMposite Autonomic Symptom Score (COMPASS) 31 questionnaire, completed the day before surgery, and using the continuous noninvasive^-^ heart rate sensor (MooKy HR memory®) applied on the chest wall the same day. The COMPASS 31 questionnaire is a validated test composed of 31 items assessing the clinical symptoms of the activity of the ANS divided into 6 domains: orthostatic intolerance (4 questions), vasomotor (3 questions), secretomotor (4 questions), gastrointestinal (12 questions), bladder (3 questions), and pupillomotor (5 questions).^[20]^ The COMPASS 31 score ranges from 0 to 100, higher score indicating more severe alteration of the ANS.^[20–22]^ The noninvasive^-^ heart rate monitoring using the MooKy HR memory® sensor will allow to quantify the activity of the NAS using the following heart rate variability metrics: the relative power of the low^-^frequency spectral band of the heart variability (LF) that is indicative of the sympathetic activity, the relative power of the high^-^frequency spectral band of the heart rate variability (HF), the ratio of LH^-^to^-^HF power (LF/HF) that is indicative of sympathetic to parasympathetic autonomic balance, and the the root mean square of successive differences between normal heartbeats (RMSSD) that is indicative of the parasympathetic activity.^[23–25]^

The MooKy HR memory® sensor will be temporarily removed during the surgery to allow the access to the surgical site. Then, the MooKy HR memory® sensor will be applied on the chest wall after admission in the ICU up to 48 hours after surgery. The postoperative activity of the ANS will be measured using the MooKy HR memory® using the same heart rate variability metrics as preoperatively. All heart rate and invasive arterial pressure values collected during the first 48 hours using the standard monitoring will be extracted from the Carescape B850 monitor and stored on a dedicated computer. The analysis of the data collected using the aHRV Analysis software (Nevrokard Izola, Slovenia) will allow the measurement of the postoperative activity of the ANS by calculating the following parameters: the standard deviation of the NN intervals (SDNN), the standard deviation of the average NN intervals for each 5 minutes segment of a 24 hours recording (SDANN), the percentage of successive RR intervals that differ by more than 50 ms (pNN50), the LF, the HF, the LF/HF and the RMSSD. SDNN, SDANN and pNN50 are indicators of the global activity of the ANS. Morever, the aHRV Analysis software (Nevrokard Izola, Slovenia) will allow to quantify the activity of the baroreflex by combining the temporal trend of the heart rate and of the invasive arterial pressure values collected using the Carescape B850 monitor within 48 hours after surgery.

### 3.8. Outcome measures

The primary outcome will be the mean difference between the preoperative (baseline) and the postoperative CV, and its 95% confidence interval, measured using the subcutaneous glucose sensor Abbott® Free Style Libre Pro.

Secondary outcomes will: the preoperative and postoperative BG variability, quantified by the preoperative and postoperative values of: the SD of BG, the CV, the MAGE, the glycemic lability index and the glycemic penalty index; the preoperative and postoperative activity of the ANS, quantified by the preoperative and postoperative values of: the COMPASS 31 score, the LF, the HF, the LF/HF ratio, the RMSSD, the SDNN, the SDANN, and the pNN50; the diabetes phenotype, described by the preoperative fasting BG and glycosylated hemoglobin values; the blood and urinary levels of biomarkers of inflammation (IL^-^2, IL^-^6, IL^-^10, TNF^-^alpha, 8^-^iso^-^prostanglandin^-^F_2*α*_) and of endothelial function [Endocan, angiopoietin^-^1 (Ang^-^1), angiopoietin^-^2 (Ang^-^2), vascular endothelial (VE)^-^cadherin]; and postoperative morbidity and mortality at day 30 after surgery. Postoperative morbidity includes cardiac arrest, stroke, cardiac arrhythmia requiring therapeutic intervention, surgical wound infection, pneumonia, renal failure requiring dialysis, sepsis, surgical revision, readmission in the intensive care unit or in hospital.

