## 1. Introduction

Blood glucose (BG) variability in diabetic and non-diabetic patients is independently associated with increased morbidity and mortality in the intensive care unit and after cardiac events.^[1–3]^ In cardiac surgery patients, BG variability is reported to be associated with severe postoperative complications – leading to an increase length of intensive care unit (ICU) stay – regardless of the quality of BG control obtained during the perioperative period.^[4–6]^

Several hypotheses have been raised to explain the deleterious effect of BG variability observed in diabetic patients. Basal state BG variability seems to depend on the diabetes phenotype and to differ between people with or without diabetes.^[7,8]^ Furthermore, some studies suggest an association between BG variability and the activity of the autonomic nervous system (ANS).^[9–13]^ Finally, other studies highlight that the deleterious effect of BG variability includes increased oxidative stress, endothelial dysfunction, and cell apoptosis.^[14–16]^ However, no study has specifically addressed this issue in cardiac surgery patients and the underlying mechanisms contributing to increased perioperative BG variability and to its deleterious impact remain unclear.

The aim of this study is to investigate whether postoperative GV could be related to preoperative GV and/or to perioperative alteration of the ANS activity in diabetic and non-diabetic cardiac surgery patients and the relationship between postoperative GV and blood and urinary level of inflammation and endothelial dysfunction biomarkers.

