### 3.12. Statistical analysis

Categorical variables will be compared using the Chi^-^square test or Fisher’s exact test. Normally distributed quantitative variables will be compared using the Student *t* test or an analysis of variance (ANOVA). Non^-^normally distributed quantitative variables will be analyzed using the non^-^parametric Wilcoxon or Kruskall^-^Wallis tests. Statistical tests for repeated measures will be used for before^-^ after comparisons (paired Student *t* test or paired Wilcoxon test, 1^-^way ANOVA with repeated measures or Friedman test).

The primary outcome will be described using the mean and the 95% confidence interval of the mean. The temporal trend of preoperative, intraoperative, and postoperative BG variability will be described by the mean and the 95% confidence interval of the mean of each variable describing BG variability and figured as boxplot. The relationship between preoperative and postoperative BG variability, between BG variability and the ANS activity and between the postoperative BG variability and the blood and urinary level of biomarkers of inflammation and endothelial function will be investigated using the Pearson or the Spearman correlation coefficient and univariate linear regression models and presented on adequate figures.

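### The primary objective is an association between baseline and postoperative glucose variability, but the primary outcome and the sample size rest on a mean change in CV; the planned association analysis is neither primary, nor sized, nor adjusted for group

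*Protocol article*

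**What the plan says.** **Aim and objective.** Section 1 says the study will "investigate whether postoperative GV could be related to preoperative GV". Section 2 states: "The primary objective is to describe the relationship between baseline (preoperative) and postoperative BG variability within 48 hours after surgery". The abstract gives the same primary objective.

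**Primary outcome.** Section 3.8 states: "The primary outcome will be the mean difference between the preoperative (baseline) and the postoperative CV", with a 95% interval. Section 3.12 adds: "The primary outcome will be described using the mean and the 95% confidence interval of the mean". The secondary outcomes in section 3.8 include the preoperative and postoperative values of each variability index. No outcome, primary or secondary, is a measure of association.

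**Sample size.** Section 3.11 bases the number of patients on the precision of the primary outcome in each group. It takes an SD of CV of 8.2 and a 95% interval for the pre-post difference no wider than 6.12, which gives 30 per group and 120 in all.

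**Association analysis.** Section 3.12 names "The relationship between preoperative and postoperative BG variability, between BG variability and the ANS activity" and a third relationship, with biomarkers. These "will be investigated using the Pearson or the Spearman correlation coefficient and univariate linear regression models". No adjustment for group is mentioned.

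**The concern.** A mean difference is the difference of two marginal means. It does not show whether patients who vary more before surgery also vary more after it, which is what sections 1 and 2 ask. A loose reading of the word relationship does not remove the mismatch, because section 3.12 itself treats the relationship as correlation and regression and handles it separately from the primary outcome.

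At stake is which result leads the report and whether the answer to the stated question is protected. As written, the headline estimate is a mean change. The association is one of several secondary analyses, open to a choice between Pearson and Spearman and between pooled and within-group estimation, with no precision attached. The groups are defined by diabetes status, insulin requirement and type of surgery. If mean variability differs between groups both before and after surgery, an unadjusted pooled correlation will partly reflect those differences rather than any link between patients' own baseline and postoperative values.

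**Working it through.** **Inputs.** From section 3.11: SD of CV 8.2, alpha 0.05, target full interval width 6.12, n = 30 per group, total 120. The article gives no expected correlation and no SD of the difference. Values of r below are assumed over a range, and the SD of 8.2 is assumed to hold at both times.

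**1. The plan's own figure.** Full width of a t-based 95% interval for one mean = 2 × t(0.975, n−1) × SD / √n. With n = 30: 2 × 2.045 × 8.2 / √30 = 6.124, which rounds to 6.12. The sample size therefore reproduces, and the study is sized for the mean change.

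**2. What the mean change can show.** With equal SDs, SD of the difference = 8.2 × √(2(1−r)). The mean difference itself contains no r; only its interval width does.

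| r | SD of difference | Width, n = 30 |
|---|---|---|
| 0 | 11.60 | 8.66 |
| 0.3 | 9.70 | 7.25 |
| 0.5 | 8.20 | 6.12 |
| 0.7 | 6.35 | 4.74 |

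Illustration with an assumed mean change of 5 CV points and n = 120: the estimate is 5.0 in every case, with 95% interval 2.9 to 7.1 at r = 0, 3.5 to 6.5 at r = 0.5 and 4.3 to 5.7 at r = 0.9. The width depends on r and both SDs together, so it is no substitute for an estimate of r.

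A side result: the planned width of 6.12 is reached only if r is at least 0.5 (equal SDs). The sizing thus takes for granted a value of the quantity the objective sets out to describe.

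**3. What a univariate pooled analysis can show.** Suppose r = 0 within every group, half the patients are diabetic (groups 1 and 2), and the diabetic and non-diabetic means differ by d within-group SDs at both times. Between-group variance and covariance are both d²/4, so pooled r = (d²/4) / (1 + d²/4).
- d = 1: 0.25 / 1.25 = 0.20
- d = 1.5: 0.5625 / 1.5625 = 0.36

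The values of d are assumed; the article gives none.

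**4. Precision of the association with the planned patients.** Fisher interval: tanh(atanh(r) ± 1.96 / √(n−3)).

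| Assumed r | n = 120 | n = 30 (one group) |
|---|---|---|
| 0 | -0.18 to 0.18 | -0.36 to 0.36 |
| 0.3 | 0.13 to 0.45 | -0.07 to 0.60 |
| 0.5 | 0.35 to 0.62 | 0.17 to 0.73 |

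These are simple-correlation intervals. A partial correlation adjusted for four groups uses three more parameters, so n−3 = 117 becomes 114. The half-width on the Fisher scale rises from 0.181 to 0.184, and at n = 120 the intervals become 0.13 to 0.46 for r = 0.3 and 0.35 to 0.62 for r = 0.5. The approximation is adequate for planning.

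**The case against.** The best reply is that section 3.12 already plans correlation and regression for this relationship, in the same patients, and lists it first among the relationships to be studied. That stands. A reader might infer from the mismatch that the trial could succeed on its primary outcome and leave its question unanswered. The article does not support this: the analysis is planned, and a descriptive study sized on precision has no success criterion to pass.

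A reader might also infer that the primary outcome is a single mean pooled over 120 patients in a fixed 30/30/30/30 mix, representing no clinical population. Sections 3.8 and 3.12 do not say that the mean is pooled, and section 3.11 sizes it in each group, which points to a mean per group.

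A third inference is that the mean change would mainly reflect the postoperative glucose and insulin regimen in section 3.5. It is plausible that the change of conditions contributes, but no figure in the article shows how much, and the point does not depend on it.

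It can fairly be said, too, that a group-adjusted slope assumes a common slope, while section 2 makes the relationship by diabetic status and type of surgery a secondary objective. This limits the remedy but does not defeat it: differing slopes can be examined under that objective, with the imprecision shown for n = 30.

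What the objection leaves untouched is that the analysis answering the primary objective is not primary, has no stated precision and is unadjusted for the groups.

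**Conclusion.** The point holds as a mismatch of designation, sizing and adjustment. The primary objective concerns an association; the primary outcome and the sample size concern a mean change, whose value is the same at any pre-post correlation. The arithmetic behind 30 per group is correct for what it sizes.

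The planned 120 patients give usable precision for a group-adjusted association (about ±0.16 around an assumed r of 0.3), whereas one group of 30 does not exclude zero at that r. An unadjusted pooled correlation could reach 0.20 to 0.36 from group means alone, if these differ by 1 to 1.5 within-group SDs at both times. These sizes rest on assumed values of r and of the group differences, and step 2 also on equal SDs at both times.

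This should be fixed, but it does not put the study in doubt: the data and most of the analysis are already planned.

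**What to change.** **Preferred.** By dated amendment before data are analysed:
- In section 3.8, make the primary outcome the slope of postoperative CV over 0 to 48 hours on baseline CV, adjusted for the four groups, with the partial correlation and its 95% interval.
- Keep the mean difference in CV, reported within each group as section 3.11 sizes it, as the first secondary outcome.
- In section 3.12, replace the univariate model for this relationship with the group-adjusted one, and examine differing slopes by group under the existing secondary objective.
- In section 3.11, state the expected precision of the association for a range of r, in all 120 patients and within a group of 30.

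**Alternative.** If the sponsor prefers to keep the present primary outcome, reword the primary objective in section 2 and the abstract as describing the perioperative change in CV, and make the group-adjusted association the first secondary outcome. This keeps the sample-size basis but moves the primary objective away from the aim in section 1.

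**Cost.** No added patients, measurements or visits. The preferred route needs a protocol and registry amendment, and changing a declared primary outcome must be dated and explained in the report. The alternative needs a smaller amendment to the text.
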